### Statistical analysis

The analysis set will consist of a full analysis set (FAS), per protocol (PP) set and safety set. The safety set will include any participants who were randomly assigned and received at least one acupuncture treatment. The FAS will include data indicating that the treatment was as close to intention to treat (ITT) as possible. In addition to the criteria of the safety set, to be included in the FAS participants have to be evaluated for the primary outcome at least once. To be included in the PP set, participants have to receive more than 6 sessions (75 %) of treatment. The FAS will be used in the main analysis. The primary outcome of our research is the difference in PI-NRS score change from the baseline to week 4 between the two groups. Sensitivity analysis will be performed by comparing the results from PP analysis and ITT analysis, and the last observation carried forward (LOCF) method will be used to handle the missing data.

For the descriptive analysis, data will be evaluated for normality and log-transformed when necessary. A two student’s t-test or a Wilcoxon rank sum test for continuous data and a chi-squared test or Fisher’s exact test for categorical data will be performed according to whether the data are normally distributed or skewed.

For a confirmatory analysis, primary efficacy endpoint, the change from baseline to week 4 in PI-NRS, will be evaluated using student’s t-test or Wilcoxon rank sum test. This result will be compared with adjusted result using an analysis of covariance (ANCOVA) with the baseline measurement of PI-NRS as a covariate, the treatment group as a fixed effect. The secondary efficacy endpoint will be evaluated using a student’s t-test or Wilcoxon rank sum test for continuous data or chi-squared test or Fisher’s exact test for categorical data. All of the statistical analyses will be performed SAS package (Version 9.4; SAS institute Inc., Cary, NC, USA) by a statistician blinded to patient allocation, and a significance level of 5 % will be used.

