#### Primary endpoint

The primary outcome is the mean change in the PI-NRS (0 = no pain and 10 = worst possible pain, 11-point Likert scale) from the baseline to 4 weeks. The PI-NRS has been widely used to assess chronic pain intensity in conditions such as chronic low back pain, fibromyalgia, osteoarthritis, diabetic neuropathy and post-herpetic neuralgia in placebo-controlled clinical trials [24]. In a previous study, the minimal clinically important change of PI-NRS score was 1.5 points in chronic neck pain patients [25]. Compared with global assessments of change in pain perception, the clinically important differences were a 30 % reduction of PI-NRS as “much improved” and a 50 % reduction of PI-NRS score as “very much improved,” regardless of disease, gender, age, study result or treatment group [24]. The participants will be instructed not to take a rescue medicine 4 h before assessing the pain intensity.

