##### Pain

The mean change of pain intensity from baseline at 1, 2, 3 weeks will be measured by the PI-NRS. Clinical relevance will be assessed using the ratio of participants in each group who reported PI-NRS scores that reduced greater than 1.5 points or 30 % and 50 % at 4 weeks from the baseline PI-NRS scores. We pre-defined the type of improvements as follows: a PI-NRS reduction of 1.5 points as minimally important; 30 % reduction from baseline as moderately important; and 50 % reduction as substantially important [26]. Therefore, in this trial, both the absolute and relative score change will be used to analyze the clinical relevance.

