### Sample size calculation

The primary outcome of our study is overall neck pain, which is measured by the PI-NRS change from baseline to 4 weeks. In chronic neck pain, the minimum clinically important difference (MCID) is a 1.5 unit change in the PI-NRS score [25]. According to a previous study [40], we assumed that the SD of PI-NRS change from baseline to 4 weeks will be 1.88 in the treatment group and 2.21 in the control group, each with a population correlation between the baseline and follow-up scores that was estimated as 0.5. In a superiority test, we assumed that the PI-NRS difference between the two groups will be 1.5, which is identical to the MCID. With a 5 % of significance level (α = 0.05, 2-sided) and 80 % power (1-ß = 0.8), the sample size was calculated as 31 participants in each group using G*Power 3.13 software (Franz Faul, Universität Kiel, Germany). Considering a 15 % drop-out rate, a total of 74 participants is needed.

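### LOCF is the only missing-data method named for the week-4 comparison, although pain is scored at all eight visits; if pain is still changing at dropout, the estimate can be biased in either direction

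*Protocol article*

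**What the plan says.** All references are to the protocol article.

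- **Endpoint and test.** Primary endpoint defines the outcome as the mean change in PI-NRS from baseline to 4 weeks. Under Statistical analysis, "the change from baseline to week 4 in PI-NRS, will be evaluated using student’s t-test or Wilcoxon rank sum test", and the result is compared with an ANCOVA that has baseline PI-NRS as covariate. Each analysis uses one week-4 value per person.
- **Analysis set.** "The FAS will be used in the main analysis". Besides meeting the safety-set rule (randomised and treated at least once), "to be included in the FAS participants have to be evaluated for the primary outcome at least once".
- **Missing data.** "the last observation carried forward (LOCF) method will be used to handle the missing data". No other method is named.
- **Sensitivity.** "Sensitivity analysis will be performed by comparing the results from PP analysis and ITT analysis".
- **Expected loss.** Under Sample size calculation: "Considering a 15 % drop-out rate, a total of 74 participants is needed". No rate is given by arm.
- **Available data.** Table 1 schedules PI-NRS at Visits 1 to 8, and the Pain section adds: "The mean change of pain intensity from baseline at 1, 2, 3 weeks will be measured by the PI-NRS".

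**The concern.** LOCF takes the last recorded score to be the score the participant would have had at week 4, and the test then treats it as if it had been observed. This is right only if pain stops changing when the participant leaves. The trial gives eight sessions over four weeks and reports change at weeks 1, 2 and 3 as separate outcomes, so an earlier score cannot be assumed to equal a week-4 score.

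If pain is still falling, a dropout is held at partial improvement, or at none if lost straight after Visit 1. When the arms lose equal shares at similar times, a true difference shrinks. When dropout or its timing differs by arm, the error can go either way, and a difference can appear where none exists. LOCF is therefore not reliably conservative.

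The PP versus ITT comparison contrasts populations. It does not vary the assumption about what unobserved week-4 scores would have been, so it does not test LOCF.

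**Working it through.** **Inputs from the article.** Target difference 1.5; SD of change 1.88 (treatment) and 2.21 (control); two-sided alpha 0.05; power 80 %; 1:1 allocation; 15 % dropout; PI-NRS at eight visits.

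**The plan's own figure.** Root-mean-square SD = √((1.88² + 2.21²)/2) = 2.052, and 1.5/2.052 = 0.731. For a two-sample t-test the noncentral t gives power 0.795 at 30 per group and 0.808 at 31, so 31 is reproduced. Then 31/0.85 = 36.5, rounded up to 37 per group, or 74 in total. With 37 complete participants per group, power would be 0.873. At 15 % dropout, 0.15 × 74 = 11.1, so about 11 participants would have a carried-forward value.

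**Assumptions that the article does not supply.** Linear improvement from Visit 1 to Visit 8; dropout unrelated to pain and spread evenly over visits; full changes of 3.0 (MMRA) and 1.5 (sham), or 2.0 in both arms for the no-effect case; dropout by arm as shown below.

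**Formula.** With full change c, dropout d, and share f of the change reached by the last visit:

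expected LOCF change = c × [1 − d(1 − f)]

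Two values of f follow from even dropout:

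- last score at Visits 2 to 7 (at least one post-baseline score): f = mean of 1/7, …, 6/7 = 0.50
- last score at Visits 1 to 7 (baseline-only participants included): f = mean of 0, 1/7, …, 6/7 = 3/7, taken as 0.43

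**Numbers put in, f = 0.50.**

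- 15 %/15 %: (3.0 − 1.5) × (1 − 0.15 × 0.5) = 1.5 × 0.925 = 1.39
- 25 % MMRA/5 % sham: 3.0 × 0.875 − 1.5 × 0.975 = 2.625 − 1.4625 = 1.16
- 5 % MMRA/25 % sham: 3.0 × 0.975 − 1.5 × 0.875 = 2.925 − 1.3125 = 1.61
- no true effect, 5 %/25 %: 2.0 × (0.975 − 0.875) = 0.20

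**Both values of f.** Rejection rates use the noncentral t with 37 per group and the SD held at 2.052.

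| True changes | Dropout MMRA/sham | LOCF difference, f = 0.50 | LOCF difference, f = 0.43 | Rejection rate |
|---|---|---|---|---|
| 3.0 vs 1.5 | 15 %/15 % | 1.39 | 1.37 | 82 % to 81 % |
| 3.0 vs 1.5 | 25 %/5 % | 1.16 | 1.12 | 67 % to 64 % |
| 3.0 vs 1.5 | 5 %/25 % | 1.61 | 1.63 | 92 % |
| 2.0 vs 2.0 | 5 %/25 % | 0.20 | 0.23 | 7.0 % to 7.6 % |
| 2.0 vs 2.0 | 15 %/15 % | 0 | 0 | 5 % |

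Simulation of whole trials, with f = 0.50 and a between-visit correlation of 0.7, gave 1.386, 1.164, 1.613 and 0.20 for the first four rows. Rejection rates were 79 %, 65 %, 91 % and 6.7 %.

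**Range over the trajectory.** If dropouts keep 70 % of their change (early improvement), the bias at 15 %/15 % is −0.07; if they keep 25 %, it is −0.17. For 25 %/5 % the range is −0.20 to −0.51, and for 5 %/25 % it is +0.07 to +0.17. With no true effect and 5 %/25 %, the spurious difference is 0.12 to 0.30 and type I error 5.7 % to 9.5 %.

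**The case against.** The strongest reply is that the harm depends on facts the article does not give. It states one dropout rate, none by arm, and no pain trajectory. At equal 15 % dropout, power stays near the planned 80 %. Early improvement makes the bias small. The figures of about 65 % power and 7 to 8 % type I error need a five-fold imbalance in dropout. This stands: the numbers illustrate what could happen and do not predict it.

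Several stronger readings are tempting, and the article does not support them.

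- **That the week-4 difference is biased and type I error is lost.** With equal dropout and timing and no true effect, the bias is zero.
- **That the sham arm will lose more people.** The Park device is used in both arms, and the sham needle is described as indistinguishable from a real one. Unequal dropout is possible, but it is not shown to be likely.
- **That the FAS definitely admits baseline-only participants.** Table 1 puts the first PI-NRS and the first treatment at Visit 1, so the wording allows it. But the evaluation is required on top of the safety-set rule and would add almost nothing if a baseline score met it. A post-baseline reading is at least as natural.
- **That a missing-not-at-random analysis was omitted.** The SAP is not shown and may contain one.

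The LOCF clause also shares a sentence with the PP versus ITT comparison and could be meant only for that. It is still the only method given; on that reading the main FAS analysis has none stated, and the sentence needs clarifying either way.

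Finally, repeated-measures models and multiple imputation rest on missing at random, which cannot be verified. That is a fair limit, but both use the scheduled intermediate scores and avoid the assumption that pain freezes at dropout.

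**Conclusion.** The point holds in conditional form. LOCF is a stated choice, not a detail left to another document, and it is a weak one here: dropout is planned for, pain may still be changing when people leave, filled-in scores are treated as observed, and the data for a better analysis are already scheduled.

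If pain is still changing at dropout, bias is to be expected in general, with size and direction unknown. Under linear improvement and evenly spread dropout, a true difference of 1.5 is estimated as about 1.37 to 1.39 with equal 15 % dropout. Across the two unequal patterns shown, the estimate runs from about 1.12 to 1.63. With no true effect and 5 %/25 % dropout, the spurious difference is 0.20 to 0.23 points. The figure nearer the truth in each pair applies if every dropout has a post-baseline score, the other if baseline-only participants are included. This should be changed before unblinding; it does not call the sample size into question.

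**What to change.** 1. Make the primary handling a mixed model for repeated measures on PI-NRS from Visits 1 to 8, with baseline, treatment, visit and treatment-by-visit terms and the treatment contrast at week 4. Alternatively, use multiple imputation from the same visits followed by the ANCOVA already planned. Both are valid under missing at random, which should be stated.
2. Keep LOCF only as a sensitivity analysis, labelled as such, and separate it in the text from the PP versus ITT comparison.
3. State whether the single evaluation required for the FAS must be post-baseline. As worded, a baseline-only participant could be admitted and, under LOCF, scored as zero change.

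The cost is revised wording and a little SAS programming, fixed before the blind is broken. No extra visits, measurements or participants are needed, and the total stays at 74.

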### Outcome measurement

The detailed outcome measurement time points are provided in Table 1.

**Table 1 Tab1:** Schedule for the treatment and outcome measurements

Visit	S	1	2	3	4	5	6	7	8
Week		1		2			3	4	
Informed consent	●								
Demographic characteristics	●								
Vital signs	●	●	●	●	●	●	●	●	●
Blood test	●								●
Medical history	●								
Inclusion/Exclusion criteria	●								
Conformity assessment	●								
Treatment expectancy questionnaire	●								
Random allocation		●							
Treatment		●	●	●	●	●	●	●	●
Prescription of rescue medicine		●							
PI-NRS		●	●	●	●	●	●	●	●
NDI		●							●
CROM		●							●
HRV		●							●
Perceived stress scale		●							●
EQ-5D		●							●
PGIC									●
Pressure pain threshold		●							●
Consumption of rescue medicine									●
Days of restricted activity		●							●
Blinding test		●							●
Safety assessment		●	●	●	●	●	●	●	●

Visit 1: within 4 weeks after screening, Visit 8: 4 weeks after Visit 1 (+6 days)

*CROM* Cervical Range of Motion, *NDI* Neck Disability Index; *PGIC* Patient Global Impression of Change, *PI-NRS* 11-point Pain Intensity Numerical Rating Scale, *S* screening visit

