##### Disability

The function change in the neck will be evaluated using the Neck Disability Index (NDI) and cervical range of motion (CROM) from baseline to 4 weeks. The NDI is the most frequently used questionnaire to evaluate cervical pain and function limitation in daily life and consists of 10 questions ranging from 0 to 50 points. A higher score indicates more severe symptoms. The reliability and validity of the Korean version of the NDI was examined in 2009 by Song et al. [27]. The CROM of flexion, extension, lateral bending and rotation will be measured by a CROM device (Performance Attainment Associates, Lindstrom, MN, USA). A previous systematic review showed that the reliability and validity of the CROM device were favorable compared with other methods for assessing CROM [28].

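### As worded, LOCF also covers secondary outcomes measured only at Visits 1 and 8, where it carries the baseline forward and scores a participant without Visit 8 data as zero change

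*Protocol article*

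**What the plan says.** The Statistical analysis section of the protocol article states that "The FAS will be used in the main analysis". Beyond randomisation and at least one treatment, entry needs little: "to be included in the FAS participants have to be evaluated for the primary outcome at least once". The PI-NRS is taken at Visit 1, and the text does not ask for a later value. Someone who leaves early therefore stays in the main analysis set.

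The sentence on the per-protocol and ITT comparison ends with the only missing-data rule in the article: "the last observation carried forward (LOCF) method will be used to handle the missing data". No outcome is named in that clause.

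For secondary outcomes, "The secondary efficacy endpoint will be evaluated using a student’s t-test or Wilcoxon rank sum test for continuous data". No other missing-data method is given for them. The Secondary endpoint section presents these outcomes as change from baseline. The Disability section, for example, has neck function "evaluated using the Neck Disability Index (NDI) and cervical range of motion (CROM) from baseline to 4 weeks".

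On timing, "The detailed outcome measurement time points are provided in Table 1". Table 1 marks:
- PI-NRS at Visits 1 to 8;
- NDI, CROM, HRV, PSS, EQ-5D, PPT and days of restricted activity at Visits 1 and 8 only;
- PGIC and rescue-medicine consumption at Visit 8 only.

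The Sample size calculation section expects losses: "Considering a 15 % drop-out rate, a total of 74 participants is needed".

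**The concern.** LOCF behaves differently depending on how many visits an outcome has. For the PI-NRS, a participant who leaves after Visit 5 keeps the change reached by then. For the seven two-visit outcomes there is nothing between baseline and Visit 8, so the carried value is the baseline itself. The change becomes exactly 0 and enters the t-test or Wilcoxon test as though it had been observed. Improving the handling of the PI-NRS would not alter this.

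Two things are at stake. With equal drop-out, the zeros dilute the group difference and understate improvement in both arms. With unequal drop-out and improvement in both arms, they shift the difference towards the arm that keeps more participants, even if the treatments do not differ. So the rule is not reliably conservative. PPT and days of restricted activity are affected, and the Background section offers both as an improvement on subjective scores that are open to bias.

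**Working it through.** **The plan's own figure.** Inputs from the Sample size calculation section: difference 1.5, SDs of change 1.88 and 2.21, two-sided α 0.05, power 80 %, drop-out 15 %.
- Pooled SD = √((1.88² + 2.21²)/2) = 2.052, and 1.5/2.052 = 0.731 SD.
- Noncentral t power is 79.5 % at 30 per arm and 80.8 % at 31, so 31 per arm is reproduced.
- 31/0.85 = 36.5, rounded up to 37 per arm and 74 in total, also reproduced.

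**Participants affected.** 0.15 × 37 = 5.6, so 5 to 6 per arm and about 11 of 74.

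**Model.** The documents give no SD or effect for the seven outcomes, so I work in SD units and borrow 0.731 SD for illustration. Let m be an arm's mean improvement with complete data (SD 1) and d the share set to zero, with drop-out unrelated to outcome. Then, per arm:
- mean = (1−d)·m
- variance = (1−d)(1+m²) − ((1−d)·m)²

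Power follows from the noncentral t with 37 per arm and the average of the two variances.

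**Equal 15 % drop-out.** The expected difference is 0.85 × the true one on any scale; here 0.85 × 0.731 = 0.621 SD. Example with sham improving by 0.7 SD:
- MMRA: m = 1.431, mean 1.2165, variance 0.85(1 + 1.431²) − 1.2165² = 1.111.
- Sham: mean 0.595, variance 0.85(1.49) − 0.595² = 0.9125.
- Common SD = √((1.111 + 0.9125)/2) = 1.006; standardised difference 0.621/1.006 = 0.618; power 75 %.

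| Sham improvement (assumed) | Power with zeros, 37 per arm |
|---|---|
| 0 SD | 80 % |
| 0.3 SD | 78 % |
| 0.7 SD | 75 % |
| 1.0 SD | 71 % |

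The comparison is 81 % with 31 observed cases per arm.

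**No true difference, unequal drop-out.** With both arms improving by m, the false difference is m × (gap in drop-out). At m = 1.0 SD it is 0.10 SD for 10 % v 20 % and 0.20 SD for 5 % v 25 %.

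| Improvement in both arms (assumed) | Type I error, 10 % v 20 % | Type I error, 5 % v 25 % |
|---|---|---|
| 0 SD | 5.0 % | 5.0 % |
| 0.3 SD | 5.2 % | 5.9 % |
| 0.7 SD | 6.1 % | 9.6 % |
| 1.0 SD | 7.1 % | 13.9 % |

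Both splits average 15 %, but the documents give only the overall rate.

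**The case against.** The strongest reply concerns scope. The LOCF clause is the second half of the sensitivity-analysis sentence, and the sentence before it defines the primary outcome. It can be read as a rule for the PI-NRS alone. The article would then give no missing-data rule for secondary outcomes, which an article may leave to the full plan. This stands as a doubt about intent. It does not remove the point, because the words set no such limit and one clarifying sentence is needed either way.

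Other replies also carry weight:
- The outcomes are not confirmatory. The Statistical analysis section keeps that term for the PI-NRS, and the Discussion calls the inflammation and stress work exploratory.
- The per-protocol set requires more than 6 sessions, so it drops most early leavers, and a distortion may show as disagreement with the FAS. This safeguard is partial: someone with 7 sessions can still lack Visit 8.
- The arithmetic assumes that those who leave would have improved like those who stay. If people leave because they did not improve, zero is nearer the truth.
- The larger figures need large improvements, and the largest also needs a very uneven split. At 0.3 SD improvement the effect is small.

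A reader might infer that the same problem covers the remaining secondary outcomes. The documents do not support that. PGIC and rescue-medicine use have no earlier value to carry. For the blood markers, the Biomarkers section (1 and 4 weeks after randomisation) and Table 1 (screening and Visit 8) disagree about the early sample, so what would be carried is unclear.

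**Conclusion.** The point holds for the text as written. For seven secondary outcomes, LOCF amounts to carrying the baseline forward, and every FAS participant without a Visit 8 value is scored as zero change. At the planned 15 % drop-out in both arms, the expected difference is 0.85 of the true one, given drop-out unrelated to outcome. That factor does not depend on the scale. The power range of 80 % to 71 % and the type I error range of 5 % to 14 % rest on the borrowed 0.73 SD effect (power only), on assumed improvements of 0 to 1.0 SD and, for type I error, on assumed drop-out splits. None of these is documented for these outcomes, and the low end shows almost no harm.

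A reader might infer that the trial's main result is compromised, or that a false-positive rate near 14 % is to be expected. Neither is supported. The PI-NRS is rated at every visit, so the primary conclusion is not touched by this point. The 14 % figure needs both a 1.0 SD improvement and a 5 % v 25 % split. The point should be settled before analysis, as a repair to secondary analyses.

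**What to change.** In the Statistical analysis section, state which outcomes LOCF applies to, and that it is not used where there is a single post-baseline visit. For those outcomes, analyse the Visit 8 value by ANCOVA with its Visit 1 value as covariate. Either use observed data, which is simpler, or multiply impute Visit 8 from arm, baseline and the PI-NRS ratings at attended visits. Keep baseline-carried-forward only as a sensitivity analysis for data missing not at random. Bring the biomarkers under the same rule once the Biomarkers section and Table 1 agree on the sampling times.

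The cost is a sentence or two and a short SAS programme. ANCOVA and SAS are already in the plan, and no new data are needed. The downsides are slightly wider intervals and an explicit missing-at-random assumption, which could overstate benefit if people leave because they did not improve. That is why the sensitivity analysis should stay.

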#### Secondary endpoint

The secondary outcomes include a change from the baseline of clinical relevance for pain (ratio of change greater than 1.5 in PI-NRS and decrease greater than 30 % and 50 % on the PI-NRS), function (NDI and Cervical Range of Motion (CROM)), autonomic and psychometric measurements (Heart Rate Variability (HRV) and Perceived Stress Scale (PSS)), quality of life (EuroQol (EQ-5D)), global assessment (Patient Global Impression of Change (PGIC)), semi-objective outcomes (pressure pain threshold (PPT), consumption of rescue medicine, days of restricted activity), immunologic and stress markers and adverse events.

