##### Autonomic and psychometric measurement

The mean change from baseline for autonomic and psychometric measurements will be assessed by heart rate variability (HRV) and perceived stress scale (PSS). HRV will be evaluated by the commercial device PowerLab Biomap ML132 (AD Instrument, Castle Hill, Australia) with a 400 Hz sampling rate. HRV measurements will be conducted according to the guidelines written by the task force of the European Society of Cardiology and the North American Society of Pacing and Electrophysiology [29]. The standard deviation (SD) of the NN interval, square root of the mean squared differences of successive NN intervals, Low frequency (LF), High frequency (HF), LF/HF ratio and Total Power will be evaluated. Developed in 1983 by Cohen [30], the PSS is a self-reported questionnaire that evaluates degree of the individual’s perceived stress with a 5 point-Likert scale consisting of 14 questions. The questionnaire was translated into Korean, and the reliability and validity of the Korean version of the PSS [31] was studied.

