##### Biomarkers

Inflammatory/immunologic and stress biomarkers will be assessed at 1 and 4 weeks after randomization. Biomarkers of inflammation such as ESR and CRP; immunologic markers such as IL-1B, IL-6, TNF-α, IFN-γ; and stress markers such as serum cortisol were chosen according to previous research [36, 37]. Blood samples were collected from 10:00 to 11:30 am to minimalize the cortisol changes throughout the day.

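### Heart rate variability and blood markers are compared without baseline adjustment, and log transformation is named only for the descriptive analysis: valid tests, but inefficient ones

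*Protocol article*

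**What the plan says.** The Statistical analysis section has two relevant paragraphs.

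- **Descriptive paragraph.** It opens with "For the descriptive analysis, data will be evaluated for normality and log-transformed when necessary". The next sentence names the t-test or Wilcoxon test and the chi-squared or Fisher test, which "will be performed according to whether the data are normally distributed or skewed".
- **Confirmatory paragraph.** The PI-NRS change is tested by t-test or Wilcoxon and then compared with an ANCOVA using baseline PI-NRS as covariate. For the other outcomes it says "The secondary efficacy endpoint will be evaluated using a student’s t-test or Wilcoxon rank sum test for continuous data". No transformation or covariate is given.

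The outcomes affected are defined elsewhere in the article:

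- For HRV, the section Autonomic and psychometric measurement says "The mean change from baseline for autonomic and psychometric measurements will be assessed by heart rate variability (HRV) and perceived stress scale (PSS". Its variables include "Low frequency (LF), High frequency (HF), LF/HF ratio and Total Power will be evaluated".
- The Biomarkers section names ESR and CRP, then "immunologic markers such as IL-1B, IL-6, TNF-α, IFN-γ; and stress markers such as serum cortisol".
- The Secondary endpoint section puts the markers in a list that begins "The secondary outcomes include a change from the baseline of clinical relevance for pain".

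The Discussion calls the work on inflammation and stress exploratory.

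**The concern.** Spectral HRV measures, their ratio, CRP and cytokines are positive quantities, and such quantities are often right-skewed. If a treatment acts on them proportionally, the raw change grows with the starting level. A few participants with high values then dominate the comparison. Moving to a rank test limits that influence but does not restore a constant effect.

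Separately, a change score uses the baseline value less efficiently than a regression on it does. The plan recognises this for PI-NRS but not for the secondary outcomes.

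The Background offers the exploration of mechanism as one of the trial's improvements on earlier work. A real proportional shift in a marker would be easier to miss than it needs to be with the data already planned.

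**Working it through.** **The plan's own figure.** Pooled SD = √((1.88² + 2.21²)/2) = 2.052, and d = 1.5/2.052 = 0.731. With the noncentral t, power is 0.795 at 30 and 0.808 at 31 per group, so 31 is reproduced. Then 31/0.85 = 36.5, rounded up to 37, gives 74 in total. This concerns PI-NRS only. No size or power is stated for any HRV or blood marker.

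**Assumed inputs.** Log-normal marker, log-SD σ of 0.3 or 0.6 to 1.0, equal at both visits; correlation r of 0.5 or 0.7 on the log scale (the article gives 0.5, but for PI-NRS only); 37 per arm; two-sided 5%. The effect is a reduction, log ratio = −0.66·σ·√(1 − r²), chosen so that log-scale ANCOVA has about 80% power.

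**Log-scale methods, by formula.**
- ANCOVA: residual SD = σ√(1 − r²), so the standardised effect is 0.66. Noncentrality = 0.66 × √(37/2) = 2.84; power 0.80.
- t-test on log change: SD = σ√(2(1 − r)), so the standardised effect is 0.66 × √((1 + r)/2), which is 0.572 at r = 0.5 and 0.608 at r = 0.7. Power 0.68 and 0.73.

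Neither result depends on σ. The variance ratio of ANCOVA to change is (1 + r)/2, that is 0.75 or 0.85.

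**Raw-change methods, by simulation** (the log-scale columns are simulated too and agree with the formulas within simulation error):

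| Log-SD | t, raw change | Wilcoxon, raw change | t, log change | ANCOVA, log |
|---|---|---|---|---|
| 0.6-1.0 | 33-55% | 45-62% | 67-75% | 79-81% |
| 0.3 | not tabulated | 62-66% | 69-75% | about 80% |

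Example: σ = 0.8, r = 0.5, ratio = exp(−0.66 × 0.8 × 0.866) = 0.63. Raw t 41%, raw Wilcoxon 52%, log-change t 68%, log ANCOVA 80%. Of the 28 points between Wilcoxon and ANCOVA, 16 come from the log step and 12 from baseline adjustment.

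With 31 completers per arm and log-SD 0.6 to 1.0, the figures are 29-49% (raw t), 43-53% (raw Wilcoxon) and 71-72% (log ANCOVA).

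**The log step alone.** With 31 per arm and the effect rescaled so that the log-change t-test has about 80% power, raw change loses 7-8 points at log-SD 0.3. At log-SD 1.0 it loses about 41 points with the t-test and 21-23 with Wilcoxon. Under no effect, the raw-change tests rejected in 3.5-5.1% of runs.

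**Two sensitivity checks** (same inputs, 37 per arm, 10,000 runs per setting).
- ANCOVA on untransformed values gives about 77% at log-SD 0.3 but only 53-57% at log-SD 1.0. With mild skew, baseline adjustment alone brings most of the gain; with strong skew both steps are needed.
- If treatment raises the marker by the same factor, Wilcoxon on raw change reaches 64-70% at log-SD 0.6 to 1.0. The log step then adds little, and most of the gain is baseline adjustment.

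**The case against.** The strongest reply is that the article never says the changes are untransformed. It names no scale for the HRV change, and differencing log values would fit its words. The biomarker section mentions only assessment times. The secondary list opens with change from baseline yet contains items that cannot be change scores, such as the global impression and adverse events. The log rule also shares a paragraph with between-group tests, so it might be meant as a general rule. Marker-level scale is ordinary analysis-plan content, and that plan is not shown. The endpoints are exploratory and no power is claimed for them.

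Much of this stands. That raw change will be tested is the plain reading, not a stated fact, and the missing list of variables to be logged is no finding. What remains is that the article does state a method for these outcomes, that the method has no baseline covariate on either reading, and that the transformation is attached to a different analysis.

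A reader might also infer that the plan would log change scores, PI-NRS, rescue dose or restricted-activity days, so that participants with zero or negative values drop out. The documents do not support that. No section proposes it, the rule applies only when necessary, and Wilcoxon is offered for skewed data.

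**Conclusion.** The point holds as one of efficiency. The stated comparison of HRV and blood markers is valid, with no inflation of type I error, but less efficient than an analysis the planned data would support. For a right-skewed marker lowered proportionally, power rises from about 45-62% (Wilcoxon on raw change) to about 80% (log-scale ANCOVA). With mild skew it rises from 62-66% to 80%, mainly through baseline adjustment.

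These sizes rest on assumed log-normality, proportional effects in the downward direction, log-SD and correlation. For an upward effect the loss is smaller, and for an effect additive on the raw scale the log step need bring nothing. It would be too strong to say that the mechanism endpoints will lose power, since no marker distribution is given. The primary endpoint and the sample size are unaffected.

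**What to change.** In the Statistical analysis section, add to the sentence on secondary endpoints: right-skewed HRV parameters and blood markers, listed by name in advance, are log-transformed at each visit before any comparison; groups are compared on the log week-4 value with the log baseline value as covariate; results are given as a ratio of geometric means with 95% CI.

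The cost is analysis wording only. Results appear as ratios instead of mean differences, and the handling of values below the detection limit must be stated. The text must also name the baseline blood sample: the Biomarkers section places the first assessment at week 1 after randomization, whereas Table 1 shows the first blood test at screening.
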